#### IMI recommendation

The IMI summarized key issues in view of more than 170 peer-reviewed published articles on myopia control, and more than 85 multidisciplinary experts contributed to reports on clinical practice, basic research, and future directions [6–8, 15]. According to these IMI reports, key information about the sample size calculation is missing in published articles, and a reasonable number of subjects per group ranges from ~ 70 to 333 children over 2 to 3 years of follow-up [15]. In particular, the sample size per group for spectacles ranges from 125 to 333 [15].

Based on the expert consensus of the reviewed articles and the statistical calculation, a sample of 300 eligible children will be required in each arm of the trial. We do not plan to stratify any subgroups.

### Randomization and masking

The research coordinator will guide the participants to perform and finish all of the examinations, go through the results, and mask the groups to which the subjects belong. In addition, the coordinator will contact individuals before their follow-up visits.

The unmasked investigator (UMI) will be responsible for group allocation (i.e., allocating all of the children into either the DIMS lens group or PALs group through the sequence generation method [a random number table] at a 1:1 allocation ratio). In addition, the UMI will also be in charge of spectacle lens fitting, aftercare, performance assessments, data recording, and answering questions from participants and their parents/gradients.

The MI will be responsible for ophthalmic assessment and data measurements, blinded to the allocation, and not allowed to handle spectacle lenses throughout the study.

In addition, to avoid accidental unmasking, the spectacles will be kept by the UMI until the subjects finish the examination by the MI. Additionally, to avoid selection bias, allocation concealment will be ensured until the participants and their parents/guardians have been recruited into the clinical trial after the individuals finish all of the baseline examinations. During the clinical trials, neither the participants (together with their parents/guardians) nor the MI will be aware of group allocation.

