### Study settings and responsibilities

Five trial sites will be involved, including Peking University People’s Hospital (PKUPH; [name], principal investigator [PI]; [name], co-PI), Peking University International Hospital ([name], sub-PI), Kunming City Maternal and Child Health Hospital ([name], sub-PI), Beijing Haidian Maternal and Child Health Hospital ([name], sub-PI), and ChuiYang Liu Hospital affiliated with Tsinghua University ([name], sub-PI). Each of the hospitals is a large center with ophthalmology clinics and optometrists, and data will be collected at each site. The primary investigators at each site compose the steering committee, which is under the leadership of PKUPH ([name], PKUPH, lead PI and chair). The steering committee will provide final approval of the protocol and any changes to the procedure during the clinical trial.

Among these sites, PKUPH will be in charge of supervising the conduct of the study, including staff training and assessment, protocol decisions and amendments, form development, data management, data analyses, and quality control. The reason for endowing PKUPH with this governance authority is that PKUPH has undertaken dozens of domestic and foreign multicenter clinical trials and thus has abundant clinical trial experience. In addition, PKUPH has a group of staff members who undertake site management organization (SMO) work, which will ensure that the clinical trial protocol will be strictly implemented at different study sites.

Coordinating responsibilities, such as data collection and recording, will be performed at all of the study sites. Subjects will be screened at each site to achieve a minimum screening percentage of 10% and a maximum percentage not exceeding 30%. All of the centers will continue to screen subjects until the target population is achieved.

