### Study design and recruitment

This is designed as a 3-year, prospective, randomized, multicenter clinical trial. Recruitment is intended to begin on 30 October 2019 and is scheduled to end on 30 October 2020. A total of 600 primary school children (aged 6–12 years) will be recruited, and each of the participants will be followed for 3 years. Randomization will be performed with a random number table, and each group (DIMS or PALs) will contain 300 subjects. The final distance prescription will be determined by a masked investigator (MI) using the cycloplegic subjective refraction measured by phoropter after the objective refraction is measured by autorefraction. The lenses will be replaced with an updated prescription when the change in SER is greater than 0.50 diopters.

Potential participants will be recruited for the clinical trials at each center through two primary processes: (1) ophthalmologist referral during daily eye disorder treatment in outpatient clinics and (2) optometrist referral from optometry clinics during myopia treatment.

All of the potentially eligible participants and their parents/guardians will be contacted by a research coordinator who will explain the study in detail to ensure that the children and their parents/guardians understand the entire clinical trial. Once they are interested, both the patients and their parents/guardians will be seen in the clinical research laboratories to sign an informed consent form. Interested participants will be invited for the eligibility and baseline assessments by the study staff. All the identifying information will be confidential. It is estimated that ten new subjects will be recruited each month, on average, at each site.

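### Allocation from a random number table sits with the unmasked investigator who also deals with families, and no stratification is planned across five sites; a centrally held, site-stratified list would be a cheap improvement

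*Protocol article*

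**What the plan says.** All places are in the protocol article.

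- **Who allocates, and how (Randomization and masking).** The UMI is responsible for "allocating all of the children into either the DIMS lens group or PALs group through the sequence generation method [a random number table"]. The ratio is 1:1.
- **What else that role does (same section).** "the UMI will also be in charge of spectacle lens fitting, aftercare, performance assessments, data recording, and answering questions from participants and their parents/gradients".
- **Concealment (same section).** "allocation concealment will be ensured until the participants and their parents/guardians have been recruited into the clinical trial", after all baseline examinations are finished. The article does not say who holds the sequence or how an assignment is released.
- **Who recruits (Study design and recruitment).** Families are "contacted by a research coordinator who will explain the study in detail". The UMI is not said to recruit, take consent or judge eligibility. The outcome measurements belong to the masked investigator.
- **Target split (Study design and recruitment).** "Randomization will be performed with a random number table, and each group (DIMS or PALs) will contain 300 subjects".
- **Stratification (IMI recommendation, within the sample size section).** "We do not plan to stratify any subgroups".
- **Sites (Study settings and responsibilities).** "Five trial sites will be involved", in Beijing and Kunming, with data collected at each. A site's share of screening is to lie between 10% and 30%.
- **Analysis (Data management and data analyses).** Repeated measures analysis of variance; no site term is named.

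**The concern.** Two features of the stated method are weaker than they need to be.

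The first is concealment. It depends on who can see the next assignment before a child is committed to the trial. The only user of the sequence whom the article names is a site investigator with contact with families. Someone in that position could, even without intent, affect when a child is put forward for allocation. The article asserts concealment but describes nothing that takes it out of that person's hands.

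The second is balance within sites. The primary outcome is the change in cycloplegic subjective refraction, which depends on the examiner, and measurements are made at each of the five sites. Sites may also differ in the progression rate of the children they enrol. With no stratification by site, and no site term in the stated analysis, such differences enter the comparison of the lenses as avoidable noise.

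**Working it through.** **Inputs.** Total 600, five sites and 1:1 allocation are from the article. Site sizes are not given, so two cases are used.

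- *Equal sites.* Study design and recruitment expects ten new subjects per site per month, with recruitment from 30 October 2019 to 30 October 2020. That gives 10 × 12 = 120 per site and 5 × 120 = 600, which reproduces the stated total.
- *Unequal sites (assumption).* The 10% to 30% limits apply to screening. If they carry over to enrolment, a site has 0.10 × 600 = 60 to 0.30 × 600 = 180 children. One set that sums to 600 is 60, 60, 120, 180, 180.

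**Model (assumption).** Simple 1:1 allocation, so the number in one arm at a site of size n is X ~ Binomial(n, 0.5). The article does not say whether the table is used this way.

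**Per site.** P(40:60 or worse) = 2 · P(X ≤ 0.4n).

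| n | 95% range in one arm | P(40:60 or worse) |
|---|---|---|
| 60 | 22 to 38 | 2 · P(X ≤ 24) = 0.155 |
| 120 | 49 to 71 | 2 · P(X ≤ 48) = 0.035 |
| 180 | 77 to 103 | 2 · P(X ≤ 72) = 0.009 |

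**At least one site 40:60 or worse.**

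- Five sites of 120: 1 − (1 − 0.0353)^5 = 0.165, about 16%.
- Sites of 60, 60, 120, 180, 180: 1 − (0.845)² × 0.9647 × (0.9911)² = 0.32.

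**What one such site does to the comparison.** Suppose the arms are 300 each and one site's mean change differs by δ from a common mean at the other sites. The comparison then shifts by δ times the difference in that site's share of the two arms.

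- Site of 60 split 24:36: (36 − 24)/300 = 0.04, so the shift is 0.04δ.
- Site of 120 split 48:72: (72 − 48)/300 = 0.08, so the shift is 0.08δ.

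The documents give no value for δ, so it is left as a multiplier. The direction of the shift is random.

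**With site-stratified permuted blocks.** With blocks of 4, the arms differ by at most 2 at a site and 5 × 2 = 10 overall (295:305 at worst). With blocks of up to 6, the limits are 3 at a site and 5 × 3 = 15 overall. The required sample size does not change.

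**The case against.** The strongest objection concerns concealment. A coordinator approaches families, the masked investigator makes the measurements, and allocation is withheld until recruitment and baseline examinations are complete. Most of the UMI's listed duties follow allocation. A reader might infer that concealment is broken or that selection bias has been shown. The article does not support that: nothing says that the UMI influences who enters. What stands is narrower. The safeguard rests on one person at the site, and the separation of roles reduces the risk without removing it.

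A reader might also infer that a random number table cannot deliver 300 per group, or can do so only by forcing the last assignments. That does not follow. Such a table can be used to draw permuted blocks or to permute a fixed list of 300 and 300, and the article never says that allocation is simple. The split is unexplained, not unattainable. Even under simple allocation, a 276:324 result keeps 4 × 276 × 324 / 600² = 99.4% of the efficiency of an equal split.

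Third, imbalance within sites is chance imbalance. The unstratified comparison remains valid, and because the endpoint is a change from baseline, a constant examiner offset cancels within each child. This is correct, and it limits the point to precision. Differences between sites in progression, and changes of examiner over three years, do not cancel.

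Fourth, the sentence on stratification stands in the sample size section and does not name site. It is nevertheless the article's only statement on stratification, and it is unqualified. Finally, the full protocol (V1.0, cited under Trial status) may describe how the list is held. The point therefore rests on the combination of roles and the absence of planned stratification, both of which the article states, and not on a missing detail.

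**Conclusion.** The point holds as a modest design improvement. The article places the random number table with an investigator who has contact with families, and it plans no stratification across five sites. Concealment is therefore less secure than it could be, and balance within sites is left to chance.

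If allocation is simple 1:1, the chance of at least one site at 40:60 or worse is about 16% with five sites of 120, the sizes that the article's own recruitment rate implies. It is about 32% under the assumed unequal sizes. The consequence is some loss of precision, not bias, and its size in dioptres cannot be given from the documents. Label: cheap improvement.

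**What to change.** Amend IMI recommendation and Randomization and masking as follows.

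1. A statistician not involved in recruitment or care generates one list in permuted blocks of varying size, stratified by site.
2. Coordinating staff hold the list, separate from the clinical teams of all recruiting sites. This must include the lead hospital's own team, because that hospital both coordinates the trial and recruits.
3. Each assignment is released to the site's UMI only after consent, eligibility and all baseline examinations are recorded.
4. Site is a factor in the primary analysis.
5. The 300 per group in Study design and recruitment is stated as approximate.

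The article gives a recruitment start of 30 October 2019 and also says that recruitment had not begun at submission. If it has begun, apply the change to all remaining allocations and leave assignments already made as they are. If the full protocol already provides for any of these steps, the article's text need only be brought into line.

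The cost is a protocol amendment resubmitted to the ethics committee, a simple release procedure, and a short delay per child. The sample size is unaffected.

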### Data management and data analyses

Data from the two groups will be presented as the mean ± SD, except for the gender and patient number in each group, which will be presented as proportions. Data from a random eye will be used for data analysis according to a random table, considering the high correlation between the two eyes of the same participant. Baseline group data will be analyzed by using unpaired *t* tests. Repeated measures analysis of variance will be used to determine changes from baseline over time and between the two study groups. Bonferroni corrections will be used for post hoc comparisons. Correlations between changes will be calculated using Pearson’s correlation coefficient.

In the present study, all randomized participants will be included in the data analysis, regardless of protocol adherence. Missing data will not be included in the following analysis and will not be imputed from the time point of dropout. An interim analysis of the primary endpoint will be performed by an independent statistician when 50% of the participants have been allocated and have completed a 6-moth follow-up examination.

Once the subjects are enrolled, retention efforts will be addressed with participants and parents/guardians. Coordinators, study investigators, and examination staff will (1) provide periodic communication about the clinical trial and myopia control strategies for the subjects, (2) provide feedback regarding the eye care data of the subjects, and (3) provide reminders of the follow-up visit and final visit.

An internal data monitoring committee (DMC) will be established and will consist of ophthalmologists who are not involved in running the trial, statistical experts, and members of the ethics committee. The DMC chair will be [name], the PKUPH ethics committee director. Data monitoring will be performed quarterly by the DMC, including monitoring for data completeness, safety information, adverse events, and so forth. No auditing will be performed through a professional organization. The integrity of the trial for each subject will be cross-checked between sites to ensure the appropriate allocation and completeness, accuracy, timeliness of data collection, and so forth.

In the present study, the main adverse event will likely be decreased visual clarity and discomfort after wearing glasses. Adverse events occurring after the dispensing of spectacle lenses will be recorded, and investigators will address the signs and symptoms of the subjects in a timely manner.

Participants may withdraw from the study for any reason at any time. In addition, the investigators may also withdraw participants from the study to protect their safety. All study-related information will be stored securely in locked file cabinets in the research laboratory at each study site. All of the records containing personal identifiers, such as names and informed consent, will be stored separately from data records identified by code number.

### Ethical approval and conduct

Ethical approval has been provided by Peking University People’s Hospital, and all amendments will be resubmitted to the ethics committee. Patient recruitment had not yet started at the time of manuscript submission.

## Discussion

### Necessity of the current study

The average age of myopia onset is 8 years in the United States and Singapore, whereas it is ~ 6–7 years in Asian countries other than Singapore [4, 17, 18]. In cases of myopia onset before the age of 8, there are not many alternative treatments, making spectacle lenses the main choice for parents and children [7, 8, 15]. Although the prominent theory of myopia control (SER and AL progression) hypothesizes that peripheral MD slows progression [9, 19, 20], evidence of the efficacy of various optical designs in children under the same inclusion criteria is lacking. Additionally, evidence has shown that the myopia control effects of plus defocus lenses are weaker and less consistent in human myopia clinical trials with spectacles [13, 14, 16, 21].

Additionally, MD spectacle lenses need to be adjusted regularly due to downward frame slippage to ensure that the child is looking through the near addition as much as possible for near vision while looking through the center for distant vision. When looking through the addition lenses, children undergo a special visual experience, which is not fully understood.

Thus, the current study aims to (1) investigate the myopia control effects of DIMS lenses and PALs through SER and AL changes in 600 children with early-onset myopia between 6 and 12 years old; (2) compare various indicators, including peripheral refraction, accommodation, contrast sensitivity, stereopsis, choroidal thickness, and wearing experience, over the course of 3 years; and (3) minimize bias through the cooperation of a multicenter and multiarea research group. The results will broaden understanding of whether and how much the different MD designs retard myopia progression.

### Principle of outcome selection

Visual function has many aspects, so it is recommended to be included in clinical trials evaluating myopia control [15]. The most common primary outcome measure in myopia control studies is refractive error, which is directly related to the tested treatment efficacy. To ensure maximal consistency of the measured results at each research center, we specified a standard method for cycloplegia (refer to the “Methods” section above).

In the present study, we chose subjective refraction measured by phoropter as the main primary outcome, not the objective refraction measured by autorefraction. For clinical application and clinical trial assessment [10], cycloplegic subjective refraction is recommended as an endpoint measurement [22], especially for the patient who has optical aberrations, such as astigmatism.

To minimize evaluation bias and help with data interpretation, several indicators related to changes in refractive error and myopia progression will also be measured, including AL, corneal curvature, peripheral refraction, parental myopia status, environmental influences, and education insensitivity. In addition, the self-report questionnaire will be used to evaluate compliance and wearing experience [23].

As mentioned before, the underlying principle through which MD can slow myopia progression is that it provides blurry images in front of the retina when objects are viewed at close range. MD may induce unexpected effects on vision, including aspects such as contrast sensitivity, stereopsis, accommodation, and convergence. Therefore, in addition to regular examination items, all of the aforementioned items will be measured in the current study.

MD has been proven to reduce myopia progression and axial elongation and has gained great interest in the context of preventive treatment for myopia, with few adverse effects seen in early childhood. The purpose of this study is to investigate the myopia control effects of two types of MD spectacle lenses over 3 years of follow-up in 6- to 12-year-old schoolchildren. The findings from the present study are proposed as a resource to inform future clinical practices.

### Trial status

Ethical approval has been obtained from Peking University People’s Hospital (protocol version number 2019PHA049-001, V1.0; dated 2019 Sept 9). Participant recruitment has not yet begun as of this submission. The clinical trial is started to recruit participants from 30 October 2019, and the approximate date when recruitment will be completed is 30 October 2020.

## Data Availability

Not applicable. Data sharing is not applicable to this article, because no datasets have been generated or analyzed in the current study. After the clinical trial is finished, the original data will be uploaded to the ResMan Primitive Data Sharing Platform (IPD Sharing Platform) of the China Clinical Trials Registry, http://www.chictr.org.cn/index.aspx.

## Abbreviations

AL: Axial length
BCVA: Best corrected visual acuity
ChiCTR: Chinese Clinical Trial Registry
DIMS: Defocus incorporated multiple segments
DMC: Data monitoring committee
IMI: Interventions Myopia Institute
MD: Myopic defocus
MI: Masked investigator
PALs: Apollo progressive addition lenses
PKUPH: Peking University People’s Hospital
SER: Spherical equivalent refraction
SMO: Site management organization
SV: Single vision
UMI: Unmasked investigator
